**Outcome** **measures**

Group 1 and 2: Outcome measures will be performed at the commencement of the trial before intervention (baseline, week-0), after 4 weeks of treatment, and at the end of the trial (12 weeks of treatment), and at 6-months (3-months of zero intervention wash out). In addition to the physiognomy measurements (weight, girth), motor coordination, balance, cognition, social cognition, smell test, carer diary and self-assessment outcome measures, participants will also be asked to provide faecal and saliva samples (for microbiome analysis) on 2 occasions; 3 samples before treatment begins and 3 samples at the end of the treatment period (12 weeks).

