**4. OBJECTIVES**

1. to determine the effect of PBMt over a 12-week period on a variety of fine and course motor symptoms
2. to determine the effect of PBMt over a 12-week period, on a cognitive function, including social cognition
3. to determine the effect of PBMt over a 12-week period, on the composition of the intestinal and oral microbiome

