**5. HYPOTHESIS**

5a. Primary Hypothesis: PBMt will have no adverse effects on PD participants

5b. Secondary Hypothesis: PBMt will reduce the symptoms of PD

5c. Tertiary Hypotheses: PBMt will alter the microbiome

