**8a. Inclusion criteria**

- Females and males aged 60–85 years
- Diagnosed with Idiopathic PD (by UK Brain Bank Criteria) with Modified Hoehn & Yahr (H&Y) Stage I-III during ON periods
- ≥3weeks of stable anti-Parkinson’s Disease medication.

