**8b. Exclusion** **criteria**

Patients will be excluded from the study, if they:

- Are not capable of self-care
- Have a cognitive impairment with Montreal Cognitive Assessment (MOCA) score of <24
- History of significant psychotic episode(s) within the previous 12 months
- History of suicidal ideation or attempted suicide within previous 12 months.
- Take potentially photosensitizing medication, especially imipramine, hypericum, phenothiazine, lithium, chloroquine, hydrochlorothiazide, or tetracycline
- have a history of structural brain disease, active epilepsy, stroke or acute illness, factors affecting gait performance and stance such as severe joint disease, orthopaedic injuries, weakness, peripheral neuropathy with proprioceptive deficits, severe peripheral vascular occlusive disease, severe musculoskeletal disorders, uncorrected vision, vestibular problems or other severe conditions that would:
  - preclude the use of PBM therapy
  - place the patient at risk during evaluation of their PD, or
  - interfere with the evaluation of their PD
- have cardiac disease
- Patients who are currently participating in other trials regarding the treatment of PD, such as advanced therapies (Duodopa, Apomorphine, DBS).

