**10b. Secondary Outcomes:**

- Course motor control (up-and-go test; timed walk; step test)
- Fine motor control (spiral test; 9-hole peg test; writing task)
- Balance (static; tandem)
- Cognition (Montreal Cognitive Assessment)
- Self-assessment (PDQ39 questionnaire; PDSS sleep scale)
- Carer diary of daily living
- Smell identification test
- Microbiome analysis

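### Antibiotic and probiotic use around the microbiome samples is neither restricted nor recorded in the visible protocol, and section 13b states no active-versus-sham contrast that would help separate it from treatment

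*Protocol*

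**What the plan says.** **Purpose.** Objective 3 (section 4) is to determine the effect of 12 weeks of treatment "on the composition of the intestinal and oral microbiome". Hypothesis 5c (section 5, tertiary) is that "PBMt will alter the microbiome", with no direction given. The secondary outcomes list "Microbiome analysis" without naming a metric.

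**Sampling.** Under Outcome measures in section 12, participants are to give "faecal and saliva samples (for microbiome analysis) on 2 occasions; 3 samples before treatment begins and 3 samples at the end of the treatment period", the latter at 12 weeks. The same paragraph begins "Group 1 and 2: Outcome measures will be performed at the commencement of the trial before intervention", so the sham group is sampled on the same schedule as the active group.

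**Medication rules.** There are two. Section 8a requires "≥3weeks of stable anti-Parkinson’s Disease medication". Section 8b excludes patients who "Take potentially photosensitizing medication, especially imipramine, hypericum, phenothiazine, lithium, chloroquine, hydrochlorothiazide, or tetracycline".

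**Analysis.** Section 13a makes baseline the reference for all outcomes. Section 13b describes the trial as a set of N=1 studies. It counts participants whose change exceeds half a baseline SD and compares those counts between time points by chi-square. The only comparison between groups that it states is with the Brisbane and Adelaide arms.

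**The concern.** Systemic antibiotics and probiotics act directly on what the samples measure. The two medication rules serve other ends: one steadies Parkinson treatment before entry, the other protects against light sensitivity. Neither is aimed at the microbiome, and neither keeps a course of a non-photosensitising antibiotic, or a probiotic, out of the interval between the two sampling occasions.

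Take a participant who has such a course in week 10. The week-12 samples would be accepted, and nothing in the visible protocol would flag them. Three samples per occasion reduce day-to-day variation, but all three carry the same exposure. Because hypothesis 5c has no direction, a shift either way could be read as support for it.

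At stake is the interpretation of one secondary outcome and one tertiary hypothesis. An analysis plan can adjust for exposure, or omit exposed samples, only if exposure was collected, and collecting it is a protocol procedure.

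**Working it through.** **1. Text check.** The plan gives no figure to reproduce, so the first step is to see where antibiotic or probiotic exposure could be controlled or recorded.

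| Place in protocol | What it covers | Antibiotics or probiotics |
|---|---|---|
| 8a Inclusion | stable anti-Parkinson medication | not mentioned |
| 8b Exclusion | photosensitising drugs as a class | tetracycline named as one example |
| 8b Exclusion | acute illness, with qualifiers | entry condition only |
| 12 Outcome measures | two sampling occasions | no washout, record or delay rule |
| 12b Measurement tools | list of tests and questionnaires | no concomitant-medication record listed |
| 13b Statistical analysis | change between time points | no handling rule |
| Appendix 8 | contingency procedures and criteria | not mentioned |

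**2. Time-point comparison (as in section 13b).** Let a share p of an arm be exposed, and let exposure shift the chosen measure by an average of s. The arm's mean change then contains p × s in addition to any treatment effect. At p = 0.05, 0.10 and 0.20 that is 0.05s, 0.10s and 0.20s. Without a contrast between arms or an exposure record, this part cannot be identified. The documents give neither s nor p.

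**3. Active-versus-sham comparison.** Inputs: n = 20 per arm (sections 6, 8 and 8c); p = 0.05, 0.10 and 0.20 (assumed); exposure independent between participants and unrelated to arm (assumed). The number exposed in each arm is then Binomial(20, p).

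- Expected number exposed per arm: 20p.
- P(at least one exposed in an arm) = 1 − (1 − p)^20.
- P(arms differ by k or more) = the sum of P(A = a) × P(B = b) over all pairs with |a − b| ≥ k.

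| Assumed p | Expected per arm | At least one exposed | Differ by 2 or more | Differ by 3 or more | Differ by 4 or more |
|---|---|---|---|---|---|
| 5% | 1 | 64% | 25% | 7% | 1% |
| 10% | 2 | 88% | 42% | 18% | 6% |
| 20% | 4 | 99% | 55% | 32% | 16% |

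The three-or-more column is the one to use. A difference of two is a lenient threshold, and the chance of at least one exposed participant says little about bias in an arm-level result. A difference of three moves the difference between arm means by 3/20 = 0.15 of s. The sham comparison thus removes the systematic part of the problem and leaves noise and a moderate risk of imbalance.

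**The case against.** A reader might infer that the protocol treats any change from week 0 to week 12 as a treatment effect. It does not say so. The trial is sham-controlled and both groups give the samples; the attribution problem arises from section 13b, not from the sampling sentence. Section 13b also counts improvement, and no microbiome metric or direction of improvement is named, so how a drug-driven shift would enter that count is itself unstated. These objections stand.

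A reader might also infer that tetracycline is the only antibiotic barred. Section 8b excludes photosensitising medication as a class and lists examples, so other antibacterials may fall under it. Tetracycline is only the one named. Antibiotics that are not photosensitising, and probiotics, remain open.

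The claim that exposure could never be recovered goes too far as well. Section 14 mentions standardised forms completed before the first assessment, and checking eligibility requires some medication history. The content of those forms and of the carer diary is not visible. What remains is that no visible text provides for recording use during the 12 weeks.

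It can be said that handling rules belong in an analysis plan. That is fair for the rule, but not for data collection, on which the rule depends.

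Lastly, omitting exposed participants from the main analysis would be a poor remedy. Exposure can arise after allocation, so excluding on it risks selection bias even when done blind and identically in both arms. That objection stands and settles the order of analyses under the fix.

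**Conclusion.** The point holds as a gap in data collection combined with an analysis that does not state the contrast the design makes available. In the comparison that section 13b describes, a shift caused by antibiotics or probiotics cannot be told apart from one caused by photobiomodulation. In an active-versus-sham comparison, exposure unrelated to arm mainly adds noise; the chance that the arms differ by three or more exposed participants is about 7%, 18% and 32% at exposure of 5%, 10% and 20%.

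Those rates are assumptions. The figures also assume that exposure is independent between participants and equally likely in both arms. They measure imbalance in exposure, not bias in the result, which would need the unknown size of the shift. The issue is confined to a secondary outcome and tertiary hypothesis, and the primary outcome is untouched. It is worth correcting because the remedy is cheap and use that goes unrecorded may be hard to reconstruct later.

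**What to change.** **Section 12, Outcome measures:** at both sampling occasions, record systemic antibiotic and probiotic use, covering a fixed look-back before baseline and the whole 12 weeks.

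**Section 13b:** base the microbiome conclusion for Objective 3 and hypothesis 5c on the active-versus-sham difference in change from baseline, in all participants. Add a sensitivity analysis that omits exposed participants (or exposed samples), with the exposure rule fixed before group codes are opened and applied identically in both arms.

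**Cost:** a short amendment, two extra questions at visits that already take place, and one additional analysis. At the assumed rates, about 1 to 4 participants per arm would drop out of the sensitivity analysis only. Everyone stays in the trial and in every other outcome, and no treatment is withheld or changed.

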**12b. Measurement tools used**

- Demographic data
- Physiognomic measurement (height and weight)
- Step test (Appendix 2)
- 10 meter walk test (Appendix 2)
- Spiral test (Appendix 2)
- Montreal Cognitive Assessment (MoCA) test (Appendix 3)
- Timed up-and-go (TUG) (Appendix 2)
- 9-hole peg board (Appendix 2)
- Static balance (feet apart, feet together, eyes open, eyes closed) (Appendix 2)
- Tandem balance (eyes open, eyes closed) (Appendix 2)
- Hand-writing assessment
- PDQ-39 questionnaire (Appendix 4)
- Parkinson’s disease sleep scale (PDSS) questionnaire (Appendix 5)
- Social cognition questionnaires (Appendix 6)
- Carer diary of daily activities (Appendix 7)
- Microbiome analysis (faecal and saliva sample)
- Heart rate variability
- Smell Identification test

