**13b. Statistical analysis**

As a series of N=1 studies, it is anticipated that only basic statistical analysis will be performed. For each outcome measure, descriptive data (mean, standard deviation) will be calculated. From this data, “minimally important difference” (MID) scores will be computed based on ½ SD of each measure. This is a common MID measure (Norman et al, 2003) based on the distribution of the participant scores at baseline and provides a sensitive indicator of significant change over time for N=1 case studies. As such, it does not suffer from a lack of statistical power that would be evident with more traditional ANOVA approaches with small sample sizes. The number of participants showing improvement (i.e., difference between two time points > MID) can be compared between time points with chi-square analyses.

Participants showing improvement in the Sydney arm of the multi-centre Parkinson’s trial will be compared to the Brisbane and Adelaide arms (chi-square analysis) in order to establish optimum PBM areas of treatment and doses regimens.

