**17. CONTINGENCY PLAN**

In the event that the currently proposed protocol is unable to proceed due to uncontrollable and/or unforeseen restrictions or regulations (such as those imposed by government or global bodies e.g., COVID-19 pandemic lockdown restrictions) that directly or indirectly affect:

1. The study site(s).
2. The participant’s ability to participate in the currently proposed study protocol.
3. The researcher’s ability to conduct the currently proposed study protocol.

Several changes constituting a new contingency protocol will be formulated and implemented to adhere to such restrictions/regulations (See Appendix 8.). A layman’s version of the contingency protocol will also be included as part of the PICF and handed to participants as part of the recruitment and consent process, including a separate clause to indicate that participants have received, read, and understood the contingency protocol. Information about recruitment for the study will be advertised on public media platforms, with contact details available for interested potential participants to contact the research team directly.

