**Appendix 8**

Contingency protocol

In the event that the currently proposed protocol is unable to proceed due to uncontrollable and/or unforeseen restrictions or regulations, the following changes will be implemented to the existing protocol constituting a new contingency protocol.

1. **Study design**
   1. Treatment will consist of home-based (in the participant’s own home) PBMt to the head and nose (either active or placebo treatment), 6 daily treatments per week for 12 weeks. Outcome measures to be supervised and data collected via the use of video link by Specialist Examiners and the Physiotherapists.
2. **Study setting/location**
3. Study location for both treatment outcome measures assessments will be changed to the participant’s own home.
4. **Inclusion criteria**
5. In addition to the inclusion criteria already stipulated, eligible participants will require:

   - Sufficient space (around 9 m^2^) to be able to perform motor assessments.
6. - Stable and sufficiently fast home-based internet connection for uninterrupted video calls and video conferencing.

   - Knowledge (self or carer) of using a phone and/or tablet applications on either IOS or Android platforms.**Study procedure**
7. In the absence of researcher/specialist-directed intervention, to ensure blinding of participants from group allocations and to reduce the change of participants inadvertently realising that they are in the sham, participants will be informed that there are 3 groups rather than 2 (Group 1: receiving red and infra-red light; Group 2: receiving infra-red light only; Group 3: receiving sham). In fact, there will remain to be 2 groups (Group 1: receiving red and infra-red light; Group 2: receiving sham).
8. **Outcome measures**
9. Outcome measures will be performed at the commencement of the trial before intervention (baseline, week-0), then after 2, 4, 6, 8, 10-weeks of treatment, and at the end of the trial (12-weeks of treatment), and at 6-months (3-months of zero intervention wash out).
10. All outcome measures will be conducted and recorded using a combination of self-reported assessment, visual assessment via video link with a specialist examiner (during live video or pre-recording by the participant).

1. **Consent process**
2. All previous in-person appointments during the consent process will now be conducted via video-link. For example:

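### The repeated smell test has no visible record of colds, nasal blockage or recent infection, so under section 13b's time-point comparison a recovery from infection would be scored as improvement (minor)

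*Protocol*

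**What the plan says.** - **Outcome.** Section 11 (item 10b) lists "Smell identification test" as one of eight secondary-outcome bullets. Section 12b lists it again, as "Smell Identification test", without an appendix reference, although most of the motor tests there point to a procedure in Appendix 2.
- **Timing.** Section 12, Outcome measures, puts the battery at "baseline, week-0), after 4 weeks of treatment, and at the end of the trial (12 weeks of treatment), and at 6-months". The battery includes "social cognition, smell test, carer diary and self-assessment outcome measures". Appendix 8 replaces the interim visit with readings "then after 2, 4, 6, 8, 10-weeks of treatment". With baseline, week 12 and 6 months that makes eight occasions, all at home.
- **Infection.** Section 8b excludes people with a history of several conditions, among them "stroke or acute illness". This applies at entry only. Section 17 mentions "COVID-19 pandemic lockdown restrictions", but only as an example of what could trigger the contingency plan.
- **Analysis.** Section 13a makes baseline the reference for all outcomes. Section 13b sets the minimally important difference (MID) at half the baseline SD. It then takes "The number of participants showing improvement (i.e., difference between two time points > MID") and compares that count between time points by chi-square. It also compares Sydney improvers with the Brisbane and Adelaide arms, which section 2 describes as completed. It does not state an active-versus-sham comparison.

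**The concern.** A smell score depends on the state of the nose on the day as well as on Parkinson's disease. I assume, since the protocol does not discuss it, that a cold, a blocked nose or a recent respiratory infection can lower the score temporarily. A participant tested in that state at baseline and recovered by week 12 would then cross the half-SD threshold without any treatment effect. One who is well at baseline and infected at week 12 could have a real gain hidden.

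The comparisons in section 13b are the ones exposed to this. A count compared between time points has no control for spontaneous recovery. The Brisbane and Adelaide trials ran earlier and are not concurrent controls for infection exposure. Section 6 starts intervention in August 2021, so at a Sydney site baseline falls in winter and week 12 in spring.

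Treatment is directed to the head and nose, so a gain in smell would be an attractive result to report. If nasal state is not noted on the test day, it cannot be reliably reconstructed afterwards, and a statistical analysis plan cannot adjust for something never collected.

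**Working it through.** The protocol gives no figure on this point to reproduce. The check has three steps.

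**1. What the scoring rule does.** Improvement means follow-up minus baseline > 0.5 × baseline SD.
- Baseline lowered by infection, follow-up clear: change is pushed up, so a false improver is possible.
- Baseline clear, follow-up lowered: change is pushed down, so a true improver may be missed.
- Stable nasal disease at both readings: no systematic change.

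Only the first case adds improvers. Infection-lowered baselines also widen the baseline SD, which alters the threshold for everyone.

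**2. Net effect on the count.** Inputs from the protocol: 20 per arm (section 8c) and the half-SD rule (section 13b). Assumptions not in the protocol: test-retest correlation r of 0.7 to 0.9; smell loss of 1 or 2 SD when affected; share affected 0%, 5% or 10% at each reading, equal in both arms; no treatment effect. There were 20,000 simulated trials per scenario, with the SD taken from all 40 baselines.

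With nobody affected and the SD known, the share improved is 1 − Φ(0.5/√(2(1 − r))):
- r = 0.7: 1 − Φ(0.645) = 25.9%
- r = 0.8: 1 − Φ(0.791) = 21.5%
- r = 0.9: 1 − Φ(1.118) = 13.2%

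The simulated values are slightly higher because the SD is estimated.

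| r | None affected | 10% at baseline, 5% at follow-up | 5% at baseline, 10% at follow-up |
|---|---|---|---|
| 0.7 | 26.2% (5.24 of 20) | 28.9% (5.77) | 25.3–25.7% (5.06–5.14) |
| 0.8 | 21.7% (4.36) | 25.1–25.2% (5.01–5.03) | 21.5–21.7% (4.29–4.34) |
| 0.9 | 13.6% (2.71) | 18.2–18.9% (3.63–3.78) | 14.5–15.1% (2.90–3.03) |

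The largest shift is 3.78 − 2.71 = +1.07 improvers per 20. The smallest is 5.06 − 5.24 = −0.18. Scenarios with equal shares at both readings (5%/5% and 10%/10%) fall between these. On 20 participants the range is roughly −1 to +5 percentage points.

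**3. Active versus sham.** In the same runs the two arms have the same expected count, for example 5.03 and 5.04 of 20 at r = 0.8, 10%/5%, loss 1 SD. Rejection by an active-versus-sham chi-square at a nominal 5% was 4.7% to 5.5% across all scenarios. Imbalance can still occur by chance. At a 10% share, the number affected per arm at one reading has SD √(20 × 0.1 × 0.9) = 1.34, and the difference between arms has SD √(2 × 1.8) = 1.90 participants. Each participant is worth 1/20 = 5 points of an arm's share.

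**The case against.** The strongest reply is the sham arm. Section 6 has both groups start in August 2021, so season and COVID-19 exposure are shared, and step 3 shows no systematic difference between arms. This stands. A reader might infer that infection would create a false active-versus-sham effect, and the design does not support that. The reply does not rescue section 13b as written, because that section compares time points and other trials. The reliance on time points affects every outcome, and a between-arm analysis would remove the systematic part for smell without any nasal question.

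A second reply is that such items belong on a case report form and the sensitivity analysis in the analysis plan, neither of which is shown. This is fair and is one reason the point is minor. The carer diary in Appendix 7 is also not shown, so one can say only that no visible section records nasal state.

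The acute-illness exclusion gives some protection at baseline. Its wording leaves unclear whether it applies to any acute illness or only to one that would preclude treatment, pose a risk or interfere with evaluation. On either reading it does not name lingering smell loss after an infection and does not reach later tests.

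Two stronger readings should be resisted. If 10–20% of participants were affected at one of two readings, a reader might infer that 2–4 of 20 per arm are misclassified in one direction. Losses and recoveries partly cancel, and many affected participants do not change category. A reader might also infer that infection is most likely under Appendix 8; the protocol says nothing of the kind, and that appendix moves participants to their own homes.

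**Conclusion.** The point holds in a limited form. The smell test is repeated, no visible section records the state of the nose or recent infection at any test, and the comparisons stated in section 13b would score recovery after an affected earlier reading as improvement. Loss of smell during the trial counts against improvement, not for it.

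The net shift is about −0.2 to +1.1 improvers per 20. It depends wholly on the assumed shares, smell loss and correlations above, and its sign depends on whether more participants are affected at baseline or at follow-up. Active versus sham would carry added noise and chance imbalance, provided allocation is unrelated to nasal state. Smell is one of many secondary outcomes, so severity is minor.

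**What to change.** 1. In section 13b, base the smell result on change from baseline in active versus sham, with all readings in the main analysis. Week 12 is the cleanest comparison, because section 14 offers sham participants active treatment after it.
2. At each smell test, record yes or no: cold or blocked nose today; respiratory infection or COVID-19 since the last test. At baseline, add any known smell disorder not due to Parkinson's disease.
3. Where practical, repeat an affected test within the same assessment period.
4. Run a sensitivity analysis without flagged readings. It should not be the main analysis: dropping post-baseline readings at 20 per arm costs precision and makes the compared groups depend on events after entry.

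The cost is a few form items, an occasional delayed test, one or two sentences in section 13b, and slightly lower precision in the sensitivity analysis only.
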